# Mobile Health–Supported HIV Self-Testing Strategy Among Urban Refugee and Displaced Youth in Kampala, Uganda: Protocol for a Cluster Randomized Trial (Tushirikiane, Supporting Each Other)

**DOI:** 10.2196/26192

**Published:** 2021-02-02

**Keywords:** adolescents and youth, implementation research, HIV testing, mobile health, refugee, Uganda

## Abstract

**Background:**

HIV is the leading cause of mortality among youth in sub-Saharan Africa. Uganda hosts over 1.43 million refugees, and more than 83,000 live in Kampala, largely in informal settlements. There is limited information about HIV testing uptake and preferences among urban refugee and displaced youth. HIV self-testing is a promising method for increasing testing uptake. Further, mobile health (mHealth) interventions have been effective in increasing HIV testing uptake and could be particularly useful among youth.

**Objective:**

This study aims to evaluate the feasibility and effectiveness of two HIV self-testing implementation strategies (HIV self-testing intervention alone and HIV self-testing combined with an mHealth intervention) in comparison with the HIV testing standard of care in terms of HIV testing outcomes among refugee/displaced youth aged 16 to 24 years in Kampala, Uganda.

**Methods:**

A three-arm cluster randomized controlled trial will be implemented across five informal settlements grouped into three sites, based on proximity, and randomization will be performed with a 1:1:1 method. Approximately 450 adolescents (150 per cluster) will be enrolled and followed for 12 months. Data will be collected at the following three time points: baseline enrollment, 8 months after enrollment, and 12 months after enrollment. Primary outcomes (HIV testing frequency, HIV status knowledge, linkage to confirmatory testing, and linkage to HIV care) and secondary outcomes (depression, condom use efficacy, consistent condom use, sexual relationship power, HIV stigma, and adolescent sexual and reproductive health stigma) will be evaluated.

**Results:**

The study has been conducted in accordance with CONSORT (Consolidated Standards of Reporting Trials) guidelines. The study has received ethical approval from the University of Toronto (June 14, 2019), Mildmay Uganda (November 11, 2019), and the Uganda National Council for Science and Technology (August 3, 2020). The Tushirikiane trial launched in February 2020, recruiting a total of 452 participants. Data collection was paused for 8 months due to COVID-19. Data collection for wave 2 resumed in November 2020, and as of December 10, 2020, a total of 295 participants have been followed-up. The third, and final, wave of data collection will be conducted between February and March 2021.

**Conclusions:**

This study will contribute to the knowledge of differentiated HIV testing implementation strategies for urban refugee and displaced youth living in informal settlements. We will share the findings in peer-reviewed manuscripts and conference presentations.

**Trial Registration:**

ClinicalTrials.gov NCT04504097; https://clinicaltrials.gov/ct2/show/NCT04504097.

**International Registered Report Identifier (IRRID):**

DERR1-10.2196/26192

## Introduction

HIV is the leading cause of death among young people globally and the main cause of death among adolescents and young people in sub-Saharan Africa [1]. In sub-Saharan Africa, half of newly infected adolescents and young people are girls [2,3]. Uganda’s 2018 HIV prevalence among adolescent girls was over double that of adolescent boys, with 14,000 young women aged 15 to 24 reporting new HIV infections compared with 5000 young men [4]. Only 53.6% of adolescent girls in Uganda know their HIV status, and this is far below the Joint United Nations Program on HIV/AIDS (UNAIDS) goal of 90% of persons living with HIV knowing their status by 2020 to achieve an AIDS-free generation [5,6]. HIV testing is a critical entry point for access to HIV prevention and control solutions, specifically access to antiretroviral therapy, which is vital for preventing onward HIV transmission [7,8].

There are more than 79.5 million forcibly displaced persons worldwide [9], and refugee and displaced persons are largely underserved by current HIV prevention strategies [10]. HIV vulnerabilities among displaced/refugee adolescents are shaped by a complex interplay of factors, including poverty, violence, host community HIV prevalence, urbanization, HIV testing and care access, and living conditions [10-12]. Uganda hosts more than 1.4 million refugees [13], with 62% aged below 18 years [14]. Kampala, Uganda’s capital city, hosts over 83,000 refugees [13], and 27% are aged 15 to 24 years [15]. It is important to explore HIV testing needs among urban refugees. There is a global trend of refugee urbanization, with refugees increasingly moving from refugee settlements to urban areas for employment and education opportunities [16-19]. Urban refugees and displaced adolescents and young people are at the nexus of HIV disparities among adolescents, displaced persons, and slum dwellers, and yet, there are knowledge gaps in the optimal HIV prevention for these groups [20,21].

HIV self-testing is a promising strategy to engage marginalized populations [20]. HIV self-testing can represent a convenient and private option, and may reduce stigma compared with clinic-based testing [21]. HIV self-testing has demonstrated acceptability, feasibility, and usability, with minimal harm, and is associated with increased HIV testing among individuals, including adolescents across Southern Africa and Malawi [20,22,23]. Mobile health (mHealth) strategies (digital media on mobile devices) have been efficacious in improving antiretroviral therapy adherence and HIV and sexually transmitted infection testing, and are relevant for the way youth learn and socialize [24-26]. In particular, two-way SMS-based mHealth interventions that are interactive and supportive have been found to be more efficacious in increasing adherence than one-way messages/reminders [27,28]. However, few studies have integrated mHealth into HIV self-testing delivery with adolescents or focused on optimal HIV self-testing delivery strategies with displaced/refugee youth.

Global HIV self-testing knowledge gaps include strategies to facilitate linkage to confirmatory testing and HIV care for persons testing positive [29]. Identifying strategies to promote linkage to HIV care is essential to realize the public health impact of HIV self-testing [30]. A recent systematic review reported a dearth of evidence-based strategies for linkage to HIV care following positive HIV self-testing results among adolescents [31]. This is an urgent knowledge gap that we aim to address with bidirectional text messaging strategies. We also aim to address the lack of evidence regarding the acceptability and feasibility of HIV self-testing among refugee and displaced persons [32]. In Uganda, HIV self-testing was feasible and acceptable; demonstrated the ability to identify new HIV diagnoses among men who have sex with men [33]; and was associated with increased recent and frequent testing among sex workers [34].

Tushirikiane, roughly translating to supporting each other in Swahili, aims to address these knowledge gaps among displaced and refugee adolescent youth in Uganda by testing a mHealth support strategy alongside HIV self-testing delivery to increase routine HIV testing uptake. The findings can be used to inform the implementation and scale-up of HIV self-testing programs with displaced and refugee adolescents across Uganda, sub-Saharan Africa, and other humanitarian contexts.

## Methods

### Study Aim and Objectives

This study aims to evaluate the feasibility and clinical effectiveness of two HIV self-testing delivery approaches (HIV self-testing intervention alone and HIV self-testing combined with a two-way supportive SMS mHealth intervention) in comparison with the standard of care in terms of HIV testing uptake among refugee and displaced youth aged 16 to 24 years in Kampala, Uganda. The specific objectives of this study are to determine the effectiveness of the interventions on the following criteria: (1) increased frequency of HIV testing; (2) increased knowledge of HIV status; (3) increased linkage to confirmatory testing (for those with an HIV positive self-test); and (4) increased linkage to HIV care (for persons testing positive for HIV in HIV self-testing and confirmatory testing). Secondary outcomes include (1) depression, (2) condom use self-efficacy, (3) consistent condom use, (4) sexual relationship power, (5) HIV stigma, and (6) adolescent sexual and reproductive health (SRH) stigma.

### Study Design

To evaluate the intervention effectiveness, we will conduct a cluster randomized controlled trial (cRCT), where informal settlements are randomized. The clusters include five informal settlements grouped into three sites that are randomized in a 1:1:1 method to one of three study arms. Although outcome data will be collected at the level of the individual, we selected cluster randomization over individual randomization because the intervention is implemented at the settlement level. A cluster randomized design addresses threats of internal validity. It reduces the possibility of experimental contamination due to the shared social and physical environments between youth in the same or nearby informal settlements [35]. Data will be collected at the following three time points: baseline enrollment into the intervention, 8 months after enrollment, and 12 months after enrollment.

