### Study Setting

This trial is being conducted in Kampala, which is the capital of Uganda. Uganda’s progressive refugee policies provide refugees and displaced persons in refugee settlements a plot of land. Yet, with the 2006 Uganda Refugee Law, refugees forgo rights to humanitarian assistance if they leave these refugee settlements [16,17]. The convergence of this law with refugee urbanization contributes to extreme poverty among Kampala’s urban refugees, creating slum environments [16,36,37]. Among Ugandan youth aged 15 to 19 years, the HIV prevalence is estimated at 4% [38]. However, among vulnerable youth living in Kampala’s informal settlements, this is estimated at 37.2% [39]. The five informal settlements selected for this study are grouped into three sites based on their proximity to one another (Kabalagala/Kansanga, Katwe/Nsambya, and Rubaga) and have been purposively chosen because these communities host many displaced/refugee persons in Kampala [16,18,36,37]. We focused on these refugee communities, largely from the Democratic Republic of Congo, Rwanda, and Burundi [13], where refugees continue to arrive, owing to similarities in socioeconomic status and living conditions, health care access, and shared languages (French and Swahili).

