### Study Population and Eligibility Criteria

A minimum of 432 youth (144 per cluster) between the ages of 16 and 24 years will be enrolled into this study and followed for 12 months. Individuals are eligible for inclusion if they meet the following criteria: (1) currently live in one of the following five informal settlements in Kampala: Kabalagala, Kansanga, Katwe, Nsambya, and Rubaga; (2) identify as a refugee/displaced person or have refugee/displaced parents; (3) are aged 16 to 24 years; (4) speak English, Swahili, Luganda, French, Kinyarwanda, or Kirundi; and (5) own a mobile phone. A brief eligibility screening (via phone, in person, or via WhatsApp) with interested participants will be conducted, asking self-reported HIV serostatus. Only participants reporting an HIV-negative status (baseline serostatus) will be eligible to participate.

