### Sample Size and Power Analysis

Cluster sizes of 130 per group (n=390) are required to have 80% power (*P*<.05) to detect a 25% difference (39% [5] vs 64% tested) in HIV testing between any two groups from three pairwise comparisons (control vs arm 1, control vs arm 2, and arm 1 vs arm 2) for an odds ratio of 1.66. We assume an intraclass correlation coefficient of 0.013 based on HIV research on condom use in sub-Saharan Africa [50]. With 10% attrition, 432 participants (144 per cluster) are required. Computations were performed using RStudio version 3.3.0 (RStudio Team), based on formulae for multiple comparisons of proportions, and adjusted for design effect [51].

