### Data Analysis Plan

Analysis and reporting will be conducted in accordance with CONSORT (Consolidated Standards of Reporting Trials) guidelines [52] (Multimedia Appendix 1). The analyst will be blinded to group allocation. A flow diagram will be used to illustrate patient flow (screening, randomization, allocation, and follow-up). Baseline data will be reported for all three arms and summarized as mean (SD) or median (first quartile, third quartile) for continuous variables and as count and number (percentage) for categorical variables. Primary analysis will involve intention-to-treat analysis (data from participants will be analyzed according to their allocation, irrespective of whether they actually received that intervention). Between-group comparisons will be performed using multilevel mixed effect logistic or linear regression models (to account for clustering), depending on which outcome is being evaluated. For these models, the intervention group will be entered as a fixed effect. The level of significance will be set at α=.05, but adjusted using the Bonferroni method for secondary outcomes [53]. The results will be expressed as odds ratios or mean differences as appropriate, accompanied by 95% CIs and *P* values. We will conduct adjusted analysis for the primary outcome (changes in HIV testing frequency) to investigate the role of various covariates in the relative effect. We will build mixed effect multilevel logistic regression models with the intervention group as the independent variable and HIV testing uptake in the past 3 months (yes/no) as the dependent variable. Covariates (eg, age) will be entered as a block. We will explore gender differences in primary and secondary intervention outcomes.

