### Strengths and Limitations of This Study

The Tushirikiane study is unique in exploring HIV self-testing feasibility and uptake among urban refugee and displaced youth in Kampala, Uganda. Little is known about the preferred HIV testing strategies in this population.

Our three-arm cRCT longitudinal design will allow us to examine changes over time and assess if HIV self-testing alone or HIV self-testing alongside an mHealth component (bidirectional supportive SMS) increases HIV testing uptake and status awareness in comparison with the standard of care.

Our cluster randomization by informal settlements (“slums”) mitigates threats to internal validity and experimental contamination due to the shared social and physical environments between youth in the same or nearby informal settlement.

The primary study limitations are loss to follow-up, missing data points, and study delays due to COVID-19.

Our research will provide gender- and age-stratified analyses, as well as an understanding of the potential added benefits of SMS support strategies alongside HIV self-testing to inform differentiated HIV testing strategies among urban refugee and displaced youth, which can be adapted for diverse contexts.

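### One site per arm: arm and site cannot be separated, and the planned mixed model cannot account for clustering at the level that was randomised

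*Protocol article*

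**What the plan says.** Study Design first describes settlements as the randomised units, then makes clear that they were grouped before allocation: "The clusters include five informal settlements grouped into three sites that are randomized in a 1:1:1 method to one of three study arms". Study Setting names the groups: five settlements "grouped into three sites based on their proximity to one another (Kabalagala/Kansanga, Katwe/Nsambya, and Rubaga".

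The counts agree with three clusters throughout. Study Population and Eligibility Criteria has "A minimum of 432 youth (144 per cluster"; the abstract has "Approximately 450 adolescents (150 per cluster) will be enrolled and followed for 12 months"; Sample Size and Power Analysis has "Cluster sizes of 130 per group (n=390) are required". The last section also assumes an ICC of 0.013, taken from condom-use research, and applies a design effect.

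The Data Analysis Plan compares arms with "multilevel mixed effect logistic or linear regression models (to account for clustering", and enters arm as a fixed effect. It does not name the level of the random effect.

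Strengths and Limitations says that randomising by settlement "mitigates threats to internal validity and experimental contamination". The main limitations listed there are attrition, gaps in the data and pandemic delays. The single cluster per arm is not among them.

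**The concern.** A cluster-randomised comparison takes its error from differences between clusters that received the same arm. Here no arm has a second site, so there is no such difference to observe. Whatever distinguishes one site from another at follow-up, other than the intervention, enters the arm contrast in full.

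The protocol tells the reader that this has been dealt with in the model. It has not. If the site variance is estimated at zero, or the site term is dropped, the P values and intervals rest on variation between individuals only. That affects every between-arm comparison, including the primary one. The Discussion links favourable findings to scale-up of self-testing, so overstated precision would matter.

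**Working it through.** **Inputs from the protocol.** Three sites, three arms, 1:1:1 (Study Design). Sites of 2, 2 and 1 settlements (Study Setting). m = 130 analysable per arm, 144 enrolled, or 150 in the abstract. ICC = 0.013, control proportion 39%, target 64%, three pairwise comparisons (Sample Size and Power Analysis).

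**The plan's own figures.** 390 / 130 = 3, 432 / 144 = 3 and 450 / 150 = 3, so cluster and arm are the same thing. 130 / 0.9 = 144.4, in line with the stated 144. The text does not give the route to 130. One route that comes close is one-sided .05 with no multiplicity: 49 x 2.677 = 131. Nothing below depends on that route; only the cluster size and the ICC are used.

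**Identifiability.**
- Site level: 3 sites - 3 arm means = 0 df. A site random intercept is aliased with arm.
- Independently of any ICC, three sites can be allocated to three arms in 3! = 6 ways. A randomisation test therefore cannot give a P value below 1/6, and any P<.05 must draw on individual-level variation.
- Settlement level: 5 - 3 = 2 df, with one arm holding a single settlement. The model can be fitted. In linear mixed-model simulations (300 runs each, so good to about 2 to 3 points), its variance estimate was about zero in 88% of runs. Type I error was 26% when the correlation sat at site level, and 13% when it sat purely at settlement level.

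**Size of a pure site difference.** SD = sqrt(2 x 0.013 x 0.39 x 0.61) = 0.079, or 7.9 points. The 95% range is 1.96 x 7.9 = ±15 points, against a target difference of 25.

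**Error rate when site variance is not captured.** Design effect DE = 1 + (m - 1) x ICC. The true standard error is sqrt(DE) times the naive one. Type I error = 2 x (1 - Φ(1.96 / sqrt(DE))).

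| m | DE | sqrt(DE) | Type I error | Coverage of 95% CI |
|---|---|---|---|---|
| 130 | 2.677 | 1.64 | 23% | 77% |
| 144 | 2.859 | 1.69 | 25% | 75% |
| 150 | 2.937 | 1.71 | 25% | 75% |

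Beta-binomial simulation with one cluster per arm gave 23.5%, 25.1% and 25.8%.

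**Sensitivity to the ICC (m = 144; ICC values assumed).** 0.001 gives 6.7%; 0.005 gives 13%; 0.02 gives 32%; 0.05 gives 49% (50% at m = 150).

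**At least one false positive among three pairwise tests (ICC 0.013).** About 46% at m = 130, 48% at 144 and 49% at 150. With no clustering at all, three unadjusted tests already give about 12%.

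**The case against.** Several points on the other side have force.

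- *The ICC is borrowed.* It comes from condom use, not HIV testing in these sites, and the communities were chosen for similar living conditions, access to care and languages. If the true ICC were 0.001, the error would be only about 7%. This stands as a limit on the size. It does not rescue the model, because the trial cannot show which ICC applies.
- *The outcome is a change from baseline.* The 23 to 25% describes a comparison at follow-up only. Baseline adjustment may remove site differences that are constant over time, so applying the full cross-sectional ICC afterwards may over-penalise. This stands. It does not remove site-by-time differences, and follow-up here spans an 8-month pause.
- *The random effect could be at settlement level.* The plan leaves this open, so a reader who infers that the analysis must collapse to ordinary individual-level regression goes too far. Such a term can be fitted with 2 df, but it does not capture site variance or restore the error rate.
- *Cluster allocation limits contamination.* This is a real benefit where young people in neighbouring settlements mix. A reader might infer that the internal-validity claim is simply false; it is the wider claim that needs qualifying.

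A reader might also infer that the sites are known to differ in clinic access, refugee mix or COVID-19 restrictions. The protocol reports no such differences, and peer navigators are partly the intervention itself. Nor is the 46 to 49% wholly due to clustering, since about 12% is ordinary multiplicity.

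**Conclusion.** The point holds. Each arm is one site, arm is fully confounded with site, and the stated model has no information on between-site variance. That much follows from the design and needs no assumption.

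The size is conditional. It rests on an ICC of 0.013, 130 to 150 participants per arm, no baseline adjustment and a test that does not capture site variance. Under those conditions, type I error is about 23 to 25% per pairwise comparison and interval coverage about 75%.

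The documents do not support the stronger inference that a positive result would be false or that the trial is uninformative. For 39% vs 64% at m = 130, the naive standard error is 0.060. Multiplied by 1.64 it is 0.098, a half-width of 1.96 x 0.098 = 19 points, so an observed 25-point difference would still exclude zero. That ceases at an ICC of about 0.027: 0.25 / (1.96 x 0.060) = 2.125, 2.125² = 4.52, and (4.52 - 1) / 129 = 0.027. The conclusion therefore turns on a quantity that the trial cannot estimate, and the reader must be told so.

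**What to change.** **Data Analysis Plan.**
- Do not rely on a site random effect, and remove the statement that the model accounts for clustering at the level of randomisation.
- Fit a baseline-adjusted arm-by-wave model with a participant random intercept.
- Multiply each between-arm standard error by sqrt(1 + (m - 1) x ICC), and base the intervals and P values on the result. The design effect inflates the variance, so its square root applies to the standard error: about 1.64 at m = 130 and 1.71 at m = 150 with ICC 0.013.
- Report results over a pre-specified range of ICCs, for example 0.001 to 0.05.
- State that inference is conditional on the assumed ICC, that the ICC may differ by outcome, and that baseline adjustment may deal with stable site differences but not with site-by-time differences.

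**Study Design and Strengths and Limitations.** Keep the contamination rationale. Add that there is one site per arm and that arm and site effects cannot be separated. List this as a main limitation, and word conclusions as differences between sites that are consistent with an intervention effect.

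**Cost.** Analysis-plan and protocol wording only. Recruitment is complete at 452, so the design cannot be changed, and no new data are needed. In the example above the half-width grows from 1.96 x 0.060 = 12 points to 19, and the claim becomes more modest.
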